## Abstract

Background: Stroke is a high burden illness and the second leading cause of worldwide disability with generally poor recovery rates. Robust benefits of hippotherapy, a novel neurorehabilitation approach, in functional recovery following various severe neurological disabling conditions has been shown. In the present study, we will analyze the effect of a hippotherapy program on the outcome of post-stroke patients in the first year post-stroke. Method: A randomized controlled clinical trial on the effectiveness of hippotherapy (4 weeks/18 weeks hippotherapy/conventional neurorehabilitation) versus conventional neurorehabilitation alone (22 weeks) will be conducted over 48 weeks. In the treated group, one-hour daily hippotherapy sessions will be exclusively conducted during the hippotherapy’s cycles, alternated with periods of conventional neurorehabilitation. A test battery will measure both the functional and psychological outcomes. The primary endpoint will be the patient’s functional independence. The secondary endpoints will measure the sensorimotor function, autonomy, and quality of life, as well as the caregivers’ quality of life. Results and conclusion: Individual brain connectome, life history and personality construct influence the brain’s functional connectivity and are central to developing optimal tailored neurorehabilitation strategies. According to our current practice, hippotherapy allows the enhancement of substantial neuroplastic changes in the injured brain with significant neurological recovery. The protocol aims to confirm those issues. Trial registration in ClinicalTrials.gov NCT04759326 accessed on 19 February 2021.

## 1. Introduction

Nearly 1.1 M Europeans suffer a stroke each year (17 M worldwide), which adds to 33 M stroke survivors [1]. Mortality is about 15% by 1 month, 25% by 1 year, and 50% by 5 years. A third of survivors experience disability (modified Rankin Scale scores 3–5) five years after having a stroke, due to physical, cognitive, and/or emotional deficits [2,3]. Much of the scientific efforts focus on medical programs involving acute care and inpatient rehabilitation. However, long-term disability often occurs and patients may continue to experience serious daily difficulties.

Outpatient neurorehabilitation programs are quite dissimilar, ranging from specialized interdisciplinary programs (involving different configurations of therapies) to limited individual therapies [4]. The need for better post-stroke care is still an issue. Indeed, the late rehabilitative phase is essential to both patients and their caregivers. Patients must receive a current continuum program instead of patchy modules of care shaped by a specific purpose with separate accountability [5]. Additionally, they need to understand the objectives of each phase of post-acute rehabilitation in different contexts and comprehend the challenges encountered at each level for the development of their empowerment and the appropriation of their future.

The notion of reaching a plateau in stroke recovery is questioned by a growing number of studies [6]. Accordingly, there is a need to design and assess therapeutic interventions in neurorehabilitation that promote sustained recovery from stroke over time [7,8]. Multidisciplinary programs need to be developed to cover the complex stroke continuum with the ultimate goal of reducing its large burden [7]. There is growing evidence that a multidisciplinary and cross-sectoral approach is pivotal to allow optimal post-stroke functional recovery [9,10].

Hippotherapy is an emerging specialized rehabilitation approach, performed on a specially trained horse via its movement at a walk, by a team of accredited health professionals (e.g., physicians, psychologists, physical therapists, occupational therapists, psychomotor therapists, and chiropractors) and equine specialists to guide the horse [11,12,13,14,15,16,17,18,19,20,21]. The horse movement at a walk is biomechanically similar to the movement of a human when walking and yields to comparable micro-adjustments of the patient’s postural muscles during hippotherapy [22]. Additionally, through multimodal inputs (sensory, exteroceptive, proprioceptive, interoceptive, and emotional), hippotherapy has a direct action on the individual’s motor capacities, as well as on his/her cognitive abilities [11,12,16,23,24,25,26,27]. During hippotherapy, the specific execution and repetition of a task are key elements of learning/strengthening/promoting a function and a robust neurorehabilitation backbone [11,12,13,14,15,16,17,18,19,20,21,23,24,25,26,27].

Hippotherapy incorporates motor, sensory, cognitive, and psychological stimulation with the goal of promoting recovery after stroke. It has been reported that emotionally empowering multimodal interventions, such as hippotherapy, can provide patients in a late post-stroke phase with life-changing experiences that can have a profound physical and psychological impact [28,29]. In a cohort of patients ranging from 10 months to 5 years post-stroke, hippotherapy showed immediate improvements in functional task and gait performances [29]. Additionally, increasing evidence suggests that rehabilitative activities in stimulating environments can provide functional improvements also in a late phase of recovery [30]. As such, therapeutic horseback riding (≥12 months after stroke) and horse simulator therapy (≥6 months after stroke) improve balance, asymmetric body-weight bearing, motor impairment of lower limbs, independence of ambulation, gait performance, and quality of life, when combined with conventional physiotherapy [31,32,33,34]. These results add to the body of knowledge about how such a program produces objective and subjective changes in stroke survivors, and how it can be used to facilitate the recovery process and enhance self-empowerment after stroke.

Existing standard procedures are not fully suitable for studying complex interventions, such as neurorehabilitation, in a clinical trial. Indeed, this comprehensive approach must be conducted according to specific ethical considerations and it is therefore inappropriate to suspend and/or delay a validated therapy and replace it with an experimental procedure alone, or to provide a true “placebo procedure” in a control group. Therefore, the study will have the following two arms: (i) a treatment arm where patients will receive 4 weeks of hippotherapy care combined with 18 weeks of conventional neurorehabilitation; and (ii) a control arm where patients will receive 22 weeks of conventional neurorehabilitation alone. The primary aim of this clinical trial is to compare the effect of neurorehabilitation through hippotherapy versus conventional care alone on the functional independence of patients in the first year post-stroke. The secondary endpoints will broaden the global evaluation of the patient outcomes and measure the impact of the program on the quality of life and burden of their close caregivers.

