## 2. Materials and Methods

### 2.1. Design

We will conduct a randomized open, prospective two-arm controlled trial with blinded clinical evaluations on the effectiveness of hippotherapy (plus conventional neurorehabilitation) versus conventional neurorehabilitation alone. Due to the nature of the clinical trial, participants will know which treatment they will receive and investigators may also be aware of the treatment modality during the patient inclusion/randomization process. In this context, a double- or single-blind procedure is not entirely appropriate/possible. In order to mitigate the effect of factors that are not related to the treatment or intervention being tested, the patient’s functional abilities and emotional sphere will be assessed by two external actors, i.e., two physiatrists associated with the Centre Hospitalier Sud Francilien (see below). These physicians will conducted blinded face-to-face clinical assessments (they have no link with the investigation staff; they do not have access to the whole eCRF; they will also be blinded to previous assessments; and patients and their caregivers will be carefully advised not to disclose the treatment modality they are following). The study will occur at the Equiphoria Institute (La Canourgue, France: https://www.equiphoria.com/en/; accessed on 8 September 2021) for the hippotherapy program and at the Neurology Service of the Centre Hospitalier Sud Francilien (CHSF Corbeil-Essonnes; https://www.chsf.fr/nos-service/medecine/neurologie/; accessed on 8 September 2021) for the conventional neurorehabilitation. Randomization will be stratified by age (18–59 years, 60–74 years, and ≥75 years), stroke type (ischemic versus hemorrhagic), and degree of disability (Rankin scores 3 or 4) to ensure the groups’ homogeneity. The randomization and anonymization of the patient will be performed automatically by an algorithm in the eCRF following the completion of the patient’s initial data at inclusion. The clinical tests will be stored (eCRF) in a secure digital platform of the external subcontractor (CRO) for delayed treatment.

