#### 2.1.2. Primary Efficacy Endpoint

The Functional Independence Measure (FIM; lasting 30–45 min) (time frame: Changes from baseline to week 22; changes from week 22 to week 48) is an 18-item 7-point Likert scale evaluating physical, psychological, and social function, indicating the amount of assistance required for each task. A final total score is obtained ranging from 18 (complete dependence/total assistance) to 126 (complete independence) [37].

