#### 2.1.4. Sample Size and Recruitment

From the related data [47], the sample-size calculation was based on a minimum reasonably significant difference in the primary outcome (Functional Independence Measure) of 22 points with a standard deviation of σ = 28.43 [48]. To detect that difference with a power of 80% using a two-sample *t*-test at a two-sided significance level of 5%, a total of 44 patients in the randomized arms (22 per arm) will be required. We will recruit 52 patients into the study, to allow for an attrition rate of around 20%.

Recruitment will be conducted during a 12-month period. The study will end when the last patient enrolled undergoes a neurological evaluation to determine the durability of functional recovery.

The end-of-treatment assessment will be completed within two weeks of the end of 22 weeks of treatment and the end-of-protocol assessment will be completed 26 weeks after the end of treatment. The protocol began in the fourth quarter of 2021 and will run through the third quarter of 2024.

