#### 2.2.2. Inclusion and Exclusion Criteria

Inclusion criteria:Age ≥ 18 years old;Ischemic or hemorrhagic acute stroke;Inclusion > 3 and ≤ 12 months post-stroke,Rankin score ≥ 3 and ≤ 4 at inclusion,Written informed consent,Affiliation to social security,Hip minimal abduction of 25 degrees bilateral with no history of hip dislocation and/or dysplasia,Certificate of non-contraindication.

Exclusion criteria:Major cognitive impairment affecting comprehension (Mini Mental State Examination test < 24 points);Global or sensory aphasia;Neurological or psychiatric co-morbidity (other than mild to moderate post-stroke depression);Evidence of uncontrolled seizures;Substance abuse;History of uncontrolled pain;History of allergic reactions to dust and/or horsehair, or severe asthma;Body weight ≥ 110 kg;Contraindications to physical activity;Inability or medical contraindication to travel to the Institute Equiphoria;History of therapeutic horse riding or hippotherapy during the last 6 months;Pregnant or lactating women;Patients participating in other biomedical research or in a period of exclusion.

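### Time from stroke to randomisation spans more than 3 to 12 months at entry, yet it would be adjusted for only if the arms are found to differ at baseline; fix it in advance as a covariate

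*Protocol article*

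**What the plan says.** All references are to the protocol article.

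- **Entry window** (2.2.2): "Inclusion > 3 and ≤ 12 months post-stroke".
- **Strata** (2.1): "Randomization will be stratified by age (18–59 years, 60–74 years, and ≥75 years), stroke type (ischemic versus hemorrhagic), and degree of disability", the last being Rankin 3 or 4. Time since stroke is not among them.
- **Covariate rule** (2.4.2): the arms are compared at baseline with non-parametric statistics. Background variables on which they are judged not comparable then enter the later analyses as covariates. Further confounder analyses are to be chosen in the light of the results.
- **Covariate named in advance** (2.3.2): only the number and type of rehabilitation sessions, which are recorded after randomisation.
- **Analysis of FIM** (2.4.2): a multilevel analysis for differences between and within groups, and Friedman's test for effectiveness on FIM.
- **Timing of FIM** (2.1.2): "time frame: Changes from baseline to week 22; changes from week 22 to week 48". Section 2.1.4 gives the week-22 visit a margin of two weeks. For the final visit it says: "the end-of-protocol assessment will be completed 26 weeks after the end of treatment".
- **Aim**: the Introduction speaks of an effect "versus conventional care alone on the functional independence of patients in the first year post-stroke"; the Abstract speaks of "the outcome of post-stroke patients in the first year post-stroke".

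**The concern.** The latest entrants are four times as far from their stroke as the earliest. The article itself treats this interval as meaningful. Its Conclusions separate the acute and sub-acute phases from a later chronic one and note that formal inpatient rehabilitation often ends by about 6 months. Time since stroke is therefore a plausible predictor of FIM gain under either treatment.

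A plausible baseline predictor is best adjusted for because it predicts outcome, not because it happens to differ between arms. The stated rule does the reverse. A non-significant baseline comparison does not show that an imbalance is harmless, and in a trial of this size such a comparison misses moderate gaps. The rule also leaves the analysis model unknown until the baseline data have been seen. At stake are some precision and a clean, pre-specified primary comparison. The validity of the randomised comparison is not at stake.

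**Working it through.** **1. Timeline (the plan's own figure).** The cycles and intervals in 2.1.1 give 2 + 9 + 1 + 9 + 1 = 22 weeks, and 22 + 26 = 48 weeks. Both reproduce.

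**2. When FIM is measured.** One month is 365.25/12/7 = 4.348 weeks, so 22 weeks = 5.06 months and 48 weeks = 11.04 months.
- Week 22: 3 + 5.06 = 8.1 to 12 + 5.06 = 17.1 months after stroke.
- Week 48: 3 + 11.04 = 14.0 to 12 + 11.04 = 23.0 months after stroke.

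**3. Chance imbalance in time since stroke.** The article gives no distribution of entry times, so this is an assumption.
- Uniform over 3–12 months: SD = 9/√12 = 2.60 months. With 22 per arm (2.1.4), SE of the difference in means = 2.60 × √(2/22) = 0.78 month. The 95% range is ±1.96 × 0.78 = ±1.5 months, and the probability of a gap above 1 month is about 20%.
- Triangular, weighted to early or to late entry: SD = 9/√18 = 2.12 months and SE = 2.12 × √(2/22) = 0.64 month.
- With 26 per arm and uniform entry: SE = 2.60 × √(2/26) = 0.72 month, and a gap above 1 month has probability about 17%.

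The article does not define when arms count as not comparable. If it means a 5% test, then under uniform entry gaps of up to about 1.5 months would pass and stay unadjusted.

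**4. What adjustment would gain.** Take σ = 28.43 from 2.1.4 as the SD of the analysed FIM outcome; the article does not say whether it refers to scores or to changes. The unadjusted SE of the arm difference is 28.43 × √(2/22) = 8.6 points. Suppose FIM gain falls by b points per month of delay. No value of b is given, so a range is shown, with uniform entry.

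| Assumed b | SD due to time since stroke (b × 2.60) | Share of variance, (b × 2.60)²/28.43² | Reduction in SE, 1 − √(1 − share) | Shift in effect at 1 SE / 1.96 SE of imbalance |
|---|---|---|---|---|
| 1 | 2.6 | 0.8% | 0.4% | 0.8 / 1.5 points |
| 2 | 5.2 | 3.3% | 1.7% | 1.6 / 3.1 points |
| 3 | 7.8 | 7.5% | 3.8% | 2.3 / 4.6 points |

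Against the 22-point target difference, the shifts at 1.96 SE are 1.5/22 = 7% to 4.6/22 = 21%. A shift of that size arises in only about one trial in twenty.

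**5. Where the covariate can go.** Friedman's test ranks repeated values within patients and has no covariate term. Of the analyses in 2.4.2, the multilevel analysis is the one for FIM that can carry the adjustment.

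**6. Why not another stratum.** There are already 3 × 2 × 2 = 12 strata for 52 patients, or 52/12 = 4.3 per stratum.

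**The case against.** The strongest reply is that nothing here is biased. Randomisation balances time since stroke in expectation, and chance imbalance is already part of the standard error. The rule in 2.4.2 would bring the variable in if the arms clearly differed, and an analysis plan that is not shown may name covariates. Most of this stands, and it limits the point to precision and pre-specification. It does not remove the point, because the article does more than stay silent: it states a rule that makes adjustment depend on observed imbalance.

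The size is also open to challenge. The 1–3 points per month is an assumption without support in the document. At 3 points, patients entering at 3 and at 12 months would differ by 9 × 3 = 27 points in expected gain, more than the 22-point target. The article also questions a recovery plateau and reports late gains. The upper end of the table is therefore generous.

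Two stronger readings are tempting, and the document does not support either.

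- *That the aim contradicts the schedule.* A reader might infer that the aim places the outcome within the first year, which no week-48 value can meet. But in both the Introduction and the Abstract the phrase follows the word for patients and naturally describes who is enrolled. That agrees with the 12-month entry limit. It is an ambiguity, not a contradiction.
- *That most end-of-treatment outcomes fall after the first year.* This is so for anyone entering after 12 − 5.06 = 6.94 months. Under uniform entry the share is 5.06/9 = 56%, but it ranged from 13% to 81% over the entry distributions tried, and the article gives none.

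**Conclusion.** The point holds as a modest improvement. The article makes adjustment for time since stroke conditional on a data-driven baseline check, although the variable covers a wide range at entry, is not stratified, and is known for every patient before randomisation. Fixing it in advance is the better method. The expected gain is small: an SE reduction of 0.4% to 3.8% for assumed slopes of 1 to 3 FIM points per month, under uniform entry and σ = 28.43, and less if entry times are more concentrated. It also protects against an unadjusted chance gap, whose standard error is 0.64 to 0.78 month with 22 per arm under the distributions in step 3. There is no evidence of systematic bias, and leaving time since stroke out of the strata is defensible. The first-year wording needs one clarifying sentence and nothing more.

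**What to change.** 1. In the statistical section, or in the analysis plan before outcome data are seen by arm, state that time from stroke to randomisation enters the between-group multilevel analysis of FIM as a continuous baseline covariate, whatever the observed balance. If baseline FIM is kept as one of the repeated responses, let the covariate's effect differ by visit, since the concern is its effect on gain. If the analysis plan already does this, bring the rule in 2.4.2 into line with it.
2. Note that Friedman's test cannot carry this adjustment.
3. Leave the eligibility window and the strata unchanged.
4. Add one sentence to the aim: the first-year phrase refers to time at entry (more than 3 and up to 12 months), with FIM measured at about 8–17 months (week 22) and 14–23 months (week 48) after stroke.

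The cost is one degree of freedom, or one per follow-up visit if the effect may vary by visit, and a sentence of text. The stroke date is already needed to check eligibility, so no new data are collected.

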## 2. Materials and Methods

### 2.1. Design

We will conduct a randomized open, prospective two-arm controlled trial with blinded clinical evaluations on the effectiveness of hippotherapy (plus conventional neurorehabilitation) versus conventional neurorehabilitation alone. Due to the nature of the clinical trial, participants will know which treatment they will receive and investigators may also be aware of the treatment modality during the patient inclusion/randomization process. In this context, a double- or single-blind procedure is not entirely appropriate/possible. In order to mitigate the effect of factors that are not related to the treatment or intervention being tested, the patient’s functional abilities and emotional sphere will be assessed by two external actors, i.e., two physiatrists associated with the Centre Hospitalier Sud Francilien (see below). These physicians will conducted blinded face-to-face clinical assessments (they have no link with the investigation staff; they do not have access to the whole eCRF; they will also be blinded to previous assessments; and patients and their caregivers will be carefully advised not to disclose the treatment modality they are following). The study will occur at the Equiphoria Institute (La Canourgue, France: https://www.equiphoria.com/en/; accessed on 8 September 2021) for the hippotherapy program and at the Neurology Service of the Centre Hospitalier Sud Francilien (CHSF Corbeil-Essonnes; https://www.chsf.fr/nos-service/medecine/neurologie/; accessed on 8 September 2021) for the conventional neurorehabilitation. Randomization will be stratified by age (18–59 years, 60–74 years, and ≥75 years), stroke type (ischemic versus hemorrhagic), and degree of disability (Rankin scores 3 or 4) to ensure the groups’ homogeneity. The randomization and anonymization of the patient will be performed automatically by an algorithm in the eCRF following the completion of the patient’s initial data at inclusion. The clinical tests will be stored (eCRF) in a secure digital platform of the external subcontractor (CRO) for delayed treatment.

#### 2.1.1. The Study’s Protocol

The protocol’s shape relies on our own clinical experience over the last decade [6,7,8,9,10,11,12,13,35]. The hippotherapy approach will comprise three cycles. The first one consists of two-week daily sessions. This first phase aims to (i) evaluate the patient’s neuro-functional capacities, and (ii) build the initial treatment taking into account the silent barriers that may exist (e.g., PTSD, fatigue, pain, and fear) and that strongly interfere with the individual’s functional outcome [36] developing ways to overcome them. After a nine-week “hippotherapy wash out” period during which the patient continues with the conventional neurorehabilitation care, an intermediate one-week daily hippotherapy cycle followed. Then, after a second nine-week “hippotherapy wash out” period, a final one-week daily hippotherapy cycle will occur. The conventional outpatient rehabilitation for each patient in the hippotherapy group will be temporarily suspended during the hippotherapy cycles. Six months after the end of the rehabilitation protocol, patients will be monitored for sustainability of functional gains. The entire protocol will last 48 weeks (see Figure 1).

The so-called “hippotherapy wash out” period has three main objectives: fixing of the new schemes; translating them to day-to-day skills; and revealing new unmet needs. Our current clinical practice supports the proposed rhythm for rehabilitation through hippotherapy (see Section 2.3.3).

A battery of validated tests are used to study the patient’s level of disability, sensorimotor function, and quality of life. A measurement of the quality of life and burden of caregivers is also included. Patients will undergo evaluations prior and at the end of the neurorehabilitation program, as well as six months after the end of the neurorehabilitation program (end of the study).

